### Sampling plan

According to the registry of the Division of Cancer Prevention and Genetics (IEO), all women with *BRCA1* and/or *BRCA2* germline mutations with at least a male relative will be reached by a phone call and/or an email. During the first contact, a member of the research team informs the female patients about the research purposes and the procedure. The researcher will then ask the women to share the information with their male relative(s) and to invite him (them) to participate in the research. All the information about the research, including an invitation letter, an information sheet, and the consent form, will be also sent by email to the women. If those relatives want to be contacted to participate in the study, a researcher calls them and shares with them the information sheet, the informed consent, and the link to the online survey (via Qualtrics^TM^ Platform). Self-referral of the male participants who have been told by their female relatives about the study will be considered as well. Participants will sign the informed consent before starting to fill the survey and data collection will be done through an online survey via the use of an identifier. Table 1 shows inclusion and exclusion criteria.

**Table 1 pone.0266327.t001:** Inclusion and exclusion criteria for the male participants.

Inclusion criteria	Exclusion criteria
Male relatives of patients with an established germline genetic mutation (pathogenic or likely pathogenic variants) of the BRCA1 and / or BRCA2 genes	*BRCA1* and / or *BRCA2* germline genetic screening load detected
Aged ≥ 18	Diagnosis of breast, pancreatic, or prostate cancer
Able to give informed consent	
Able to read, speak, and understand Italian	

Note: ^a^ = this criterion was not present in the study protocol approved by the Ethical Committee.

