### Randomization

Participants who meet the study inclusion criteria will be randomly assigned to receive one of the two conditions. Fig 3 shows the way that participants will flow through the three assessment points for the study (Time 1, T1; Time 2, T2, Time 3, T3). Randomization will occur during T1, immediately after the data collection of psychological measures. The participants will not be informed of the condition to which they have been allocated.

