### Statistical analyses

Data exclusion: The answers to the manipulation check will be analyzed before the main analyses to see whether participants have read the message until the end, understood, and recalled the content.

Missing data: presence of missing data will be checked before conducting the main analyses. If a subject does not complete T1 and T2 that subject will be excluded from the analysis.

Normality of the data will be checked before conducting the main analyses. Non-normality will be handled applying either non-parametric tests or SEM with estimator for non-normal distribution.

Statistical analyses will be performed in SPSS version 25 and the *Lavaan* and *SemPaths* packages in RStudio software.

Preliminary analysis: Pearson’s r correlations among variables.

Main analyses: the hypotheses 1, 2, 3, and 4 will be tested either using structural equation modeling (SEM) or multiple regressions. Research question 1 will be tested either using structural equation modeling (SEM) or ANOVA. In case of non-normality in the data, WLSMV will be applied and the Satorra-Bentler scaled test statistic and robust standard errors were used. In the model specification, the factor loading of the first indicator of each latent variable will be set to 1. The following goodness-of-fit indices will be used to evaluate model-data correspondence: the Chi-square value, the Comparative Fit Index (CFI), and the Root Mean Square Error of Approximation (RMSEA). The model will be considered as acceptable when the CFI is higher than .90 and close to .95 and when the RMSEA is .08 or less. Finally, modification indices and the matrix of standardized correlation residuals will be inspected for potential improvement of model fit. Direct, indirect (or mediate), and total effects were also estimated. To test hypothesis number 5 an ANCOVA will be applied.

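### Several men from one family may enrol, but the models named for H1–H4 and RQ1 do not allow for it, so their standard errors will be too small if relatives are positively correlated

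*Protocol article*

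**What the plan says.** **Recruitment (Sampling plan).** All registry women carrying a mutation and "with at least a male relative will be reached by a phone call and/or an email". The researcher will then "ask the women to share the information with their male relative(s) and to invite him (them) to participate in the research". There is also a second route: "Self-referral of the male participants who have been told by their female relatives about the study will be considered as well". Neither this section nor Table 1 limits enrolment to one man per woman or per family, and two carriers from the same family may both be approached. On linkage, the section says only that "data collection will be done through an online survey via the use of an identifier".

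**Allocation (Randomization).** The unit is the individual man: "Participants who meet the study inclusion criteria will be randomly assigned to receive one of the two conditions".

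**Analysis (Statistical analyses).** For the determinants, "the hypotheses 1, 2, 3, and 4 will be tested either using structural equation modeling (SEM) or multiple regressions". Research question 1 uses SEM or ANOVA. For the message comparison, "To test hypothesis number 5 an ANCOVA will be applied". The covariates listed for H1–H4 are demographic and health-status variables. Robust standard errors appear once, as the response to non-normal data: "WLSMV will be applied and the Satorra-Bentler scaled test statistic and robust standard errors were used".

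**Objectives (Primary and secondary outcomes).** The message comparison is primary. The determinants of intention and action are secondary.

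**The concern.** Brothers, sons or cousins of one index woman share the familial mutation, her illness and the family's cancer history. The article's own rationale for the family-referred message is that relatives and perceived family obligations shape men's decisions about testing. It is therefore plausible that risk perception, outcome expectations, intention and uptake are positively correlated among men of one family.

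The named models, in their usual form, compute standard errors as if each man were an independent observation. A correction for non-normality does not remove dependence between men. When predictor and outcome are both correlated within families, the reported standard error of a slope is too small, confidence intervals are too narrow, and determinants of intention, planning or action would be declared more often than the nominal 5% allows.

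**Working it through.** **The plan's own figure.** The plan gives none for clustering: no design effect, no expected number of men per family, no ICC. Its power calculation concerns the message comparison, which is a different question. The planned total of 264 men is used below.

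**Inputs.** N = 264 (Sample size and power calculation) and two-sided alpha 0.05. The article gives alpha as .05 without stating sidedness. Three inputs are assumptions: m, the number of men per family; ICCx, the within-family correlation of the predictor; and ICCy, that of the outcome after adjustment for the other terms in the model.

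**Formulas for a regression slope, equal family sizes.**
- Design effect: D = 1 + (m − 1) × ICCx × ICCy
- True SE ÷ reported SE: √D
- Shortfall of the reported SE: 1 − 1/√D
- Actual type I error: 2 × [1 − Φ(1.96/√D)]

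**Example.** For m = 3 and both ICCs 0.3, D = 1 + 2 × 0.3 × 0.3 = 1.18 and √D = 1.086. The reported SE is 1 − 1/1.086 = 8% too small. Type I error is 2 × [1 − Φ(1.96/1.086)] = 7.1%.

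The last column is a simulation of ordinary least squares with 264 men treated as independent, 8,000 replicates per scenario.

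| m | ICCx | ICCy | D | True ÷ reported SE | Reported SE too small by | Type I error, formula | Type I error, simulated |
|---|---|---|---|---|---|---|---|
| 1.5 | 0.3 | 0.3 | 1.045 | 1.02 | 2% | 5.5% | not run |
| 2 | 0.3 | 0.3 | 1.09 | 1.04 | 4% | 6.0% | 6.1% |
| 3 | 0.3 | 0.3 | 1.18 | 1.09 | 8% | 7.1% | 7.2% |
| 3 | 0.5 | 0.5 | 1.50 | 1.22 | 18% | 11.0% | 11.2% |
| 2 | 1 | 0.3 | 1.30 | 1.14 | 12% | 8.6% | 8.6% |
| 3 | 1 | 0.5 | 2.00 | 1.41 | 29% | 16.6% | 16.3% |

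The last two rows are bounds: ICCx = 1 means that every man in a family has the same predictor value.

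**Message comparison (H5).** Allocation is made man by man, so arm has no within-family correlation. With ICCx = 0 the formula gives D = 1 whatever the outcome ICC. In simulation (m = 2 or 3, outcome ICC 0.1, 0.3 or 0.5) the type I error for arm was between 4.5% and 5.3%. The Monte Carlo standard error at 5% is √(0.05 × 0.95/8000) = 0.24 percentage points, so this is compatible with the nominal level.

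**The case against.** The strongest reply is that the effect is conditional and may be small. If most families contribute one man, or the correlations are low, type I error stays near 5–6%. The relevant outcome correlation is the residual one, which adjustment for the predictors and covariates may reduce. This stands, and it is why the point is worded with an if. A reader might infer that the standard errors certainly are too small, but the documents give no figure that would establish this.

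A second reply concerns the largest figures. The 8.6% and 16.6% rows need a predictor identical for all men of a family. The predictors listed for H1–H4 and RQ1 are individual self-report scales, and the Introduction describes intolerance of uncertainty as a personal trait. This also stands: those rows are bounds, not expectations. Nor should a 1.41-fold inflation be read as a reported standard error 41% too small; the shortfall is 29%.

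A third reply is that clustered standard errors belong in an unseen analysis plan, and that the identifier mentioned might already link relatives. Neither can be ruled out. But the article does more than stay silent. It fixes an enrolment route that produces related men, then names the models, the covariates and the purpose of its robust standard errors, and none of these addresses that dependence. Among the listed demographic items, neither degree of relationship nor household composition identifies which men belong to the same family.

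**Conclusion.** The concern holds in conditional form. Followed as written, the plan will understate the standard errors for H1–H4 and RQ1 if several men per family enrol and both predictors and residual outcomes are positively correlated within families. For partly shared predictors, the assumed range runs from a true standard error about 1.04 times the reported one (type I error about 6%) to about 1.22 times (11%), with an upper bound of 1.41 times (about 17%). Men per family and both ICCs are assumptions throughout. The formula is for a linear slope with equal family sizes, so it is only a guide for SEM paths, for the comparison in RQ1 and for action initiation as an outcome.

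A reader might also infer that the trial's main result is compromised. The documents do not support that: H5 rests on individual randomisation, and its error rate is essentially unchanged. The point concerns secondary analyses. It should be corrected, but it does not threaten the primary comparison.

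**What to change.** 1. At enrolment, store the index woman's study identifier with each man's record as a family ID, and give carriers from the same family a common code. This should be settled before data collection: the Ethical considerations section says the data will be analysed in anonymous form, so the link may not be recoverable later.
2. For the H1–H4 and RQ1 regressions and SEM, use standard errors clustered by family. Where the chosen SEM estimator (for example WLSMV) does not support clustering, use a bootstrap that resamples whole families. With 264 men there would be 264/2 = 132 families at two men each, or 264/3 = 88 at three.
3. For H5, a family-clustered version is optional, as a sensitivity analysis.
4. Report the number of families and the distribution of men per family, so that readers can judge how much this mattered.

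The cost is one extra variable, slightly wider intervals for the secondary hypotheses, and a little more analysis work, chiefly if the bootstrap is needed.

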### Sample size and power calculation

Participants will be 264 males, relatives of women with BRCA1 and/or BRCA2 germline mutations who are patients of the Division of Cancer Prevention and Genetics at the European Institute of Oncology (IEO) in Milan. The IEO is a specialized Hospital and an internationally recognized Cancer Center located in Italy working on research, prevention, diagnosis, and treatment of cancer.

The sample size is determined through an a priori power analysis using GPower 4.0 [51]. Among the imputed parameters it was chosen to include partial η2 = .05, alpha lower than .05, power d (1-B) = .70. Considering that Luszczynska et al. [52] found a η2 = .01, η2 = .05 is a prudential choice. Two groups, corresponding to the two experimental conditions of the study, and 7 covariates were included. The final estimated number of participants is 132, 66 in each group. It should be noted that changing the number of covariates does not change the total number of participants. As of the date of submission of this research plan for preregistration, the data have not yet been collected, created, or realized.

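### The planning effect of η² = .05 is justified as cautious by citing a smaller effect (.01); as printed, the justification runs backwards and the stated power of .70 does not extend to the cited effect

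*Protocol article*

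**What the plan says.** All of the following is in the protocol article.

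- *Sample size and power calculation* gives the inputs as "partial η2 = .05, alpha lower than .05, power d (1-B) = .70".
- The next sentence justifies the effect size: the cited study "found a η2 = .01, η2 = .05 is a prudential choice". No other quantitative support for .05 is offered.
- The model behind the calculation is described as follows: "Two groups, corresponding to the two experimental conditions of the study, and 7 covariates were included".
- The result is "The final estimated number of participants is 132, 66 in each group". The same section opens with "Participants will be 264 males".
- *Primary and secondary outcomes* makes the family-referred versus self-referred comparison (hypothesis 5) the primary hypothesis. *Statistical analyses* assigns its test: "To test hypothesis number 5 an ANCOVA will be applied".
- On missing data, *Statistical analyses* says: "If a subject does not complete T1 and T2 that subject will be excluded from the analysis". Under *Measures*, men who fail the manipulation check are also excluded. No rate is given for either loss.

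**The concern.** A cautious planning effect lies at or below the evidence, because a smaller effect demands more participants. Here the only evidence cited is .01 and the plan uses .05, yet the choice is presented as the careful one. The number and the word that describes it point in opposite directions.

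This is the only power statement in the article, and it serves the primary hypothesis. Both arms receive a first-person, gain-framed story with a shared introduction, and only the self or family referent differs. A modest difference is therefore quite possible. A reader who is told that the effect size was chosen prudently would expect the trial to be able to detect an effect of the size reported in the cited work. If it cannot, a non-significant result says much less about the two messages than that reader would suppose.

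**Working it through.** **Inputs.** From *Sample size and power calculation*: planning partial η² = .05, cited η² = .01, alpha .05, target power .70, two groups, seven covariates, calculated N = 132 (66 per group), planned N = 264. Sidedness is not stated. The ANCOVA F test with one numerator degree of freedom is two-sided, so that is used. No exclusions are modelled, since no rate is given. The cited .01 is treated as a partial η².

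**Formulas.** f² = η²/(1 − η²). Noncentrality λ = N·f². Power = P(F′ > F_crit), where F′ is noncentral F with df1 = 1, df2 = N − 2 − 7 and noncentrality λ. For two equal groups d = 2f.

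**Step 1: the protocol's own figure.** At η² = .05, f² = .05/.95 = .0526, f = .229 and d = 0.46. The smallest N giving power .70 is 120 (λ = 120 × .0526 = 6.32, power .702). The printed 132 is not reproduced from the stated inputs. Using 0, 1 or 7 covariates does not change the 120. This is a separate point and does not affect what follows.

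**Step 2: power at the planning effect and at the cited effect.** At η² = .01, f² = .01/.99 = .0101, f = .1005 and d = 0.20.

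| η² | N | λ = N·f² | Power |
|---|---|---|---|
| .05 | 132 | 6.95 | .74 |
| .05 | 264 | 13.89 | .96 |
| .01 | 132 | 1.33 | .21 |
| .01 | 264 | 2.67 | .37 |

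The normal approximation agrees at .01 (.21 and .37). A one-sided test at .05 would give .31 and .49.

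**Step 3: size of the gap.** On the η² scale, .05/.01 = 5. On the f or d scale, .229/.1005 = 2.3.

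**Step 4: N needed at the cited effect.** Power .70 at η² = .01 needs 613 men, and power .80 needs 779.

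**Step 5: smallest detectable effect.** Solving for η²:

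- N = 264: .023 for power .70 (d about 0.31), .029 for power .80.
- N = 132: .045 for power .70.

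All of these exceed .01.

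**Step 6: if the cited .01 is an ordinary η².** The protocol writes partial η² for its own value but plain η² for the cited one. If covariates explain a share R² of the variance, the matching partial value is .01/(1 − R²). The protocol gives no R², so the range below is assumed.

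| Assumed R² | Partial η² | Power at N = 264 |
|---|---|---|
| 0 | .010 | .37 |
| .30 | .014 | .50 |
| .50 | .020 | .64 |

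To reach .05 this way, R² would have to be 1 − .01/.05 = .80.

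**The case against.** The strongest reply is that the protocol makes no false power claim. It states .70 at .05, and at .05 the design gives .74 or .96. A reader might infer from the table that the trial's true power is 21% to 37%. The documents do not support that: those figures hold only if the cited value is the real effect for this contrast, and nothing shows that it is. This objection stands, and the point is limited accordingly.

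Second, the sentence would make sense if the cited study had found more than .05, so the .01 may be a misprint. The source is not available here. This also stands: the value must be checked before the text is rewritten. Either way the sentence is wrong as printed.

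Third, .01 may not be a partial η². Step 6 shows that this could raise power at 264 to .50 or .64 under the assumed values of R². It does not turn .05 into a cautious choice unless covariates explain about 80% of the variance.

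Fourth, the lower figure of .21 uses the calculated 132, whereas enrolment is planned at 264. That is fair. The figure to quote first is .37, before any exclusions.

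Fifth, it would be too strong to say that nothing supports a larger effect. The introduction cites qualitative work in which family concerns dominated men's thinking about testing. That work supports the direction of hypothesis 5 but gives no size.

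Finally, a reader might infer that the protocol intends to read a null result as equivalence. It does not say so; hypothesis 5 is a directional superiority hypothesis. The risk lies in later interpretation.

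**Conclusion.** The point holds as an error of justification. As printed, .05 is larger than the effect cited in its support, so the choice is optimistic and the argument for it is reversed. The computed power of .70 is not contradicted at the effect for which it is claimed.

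Conditional on .01 being correct and a partial η², with two-sided alpha .05 and no exclusions, power is about .37 at the planned 264 and .21 at 132. Exclusions would lower both. The trial at 264 can detect an η² of about .023 with power .70, which is still more than twice the cited value. The direction of the error is the same at 120, 132 and 264. It matters because it concerns the effect size behind the only power statement for the primary hypothesis, and so what a non-significant result can support.

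**What to change.** 1. Check the cited study for the value, the contrast it refers to, and whether it is a partial η².
2. If .01 is a misprint and the true value exceeds .05, correct the number; the description as prudential can then stay.
3. If .01 stands:
   - remove *prudential* and state that the planning effect exceeds the cited one;
   - report power at both values for the chosen N (at 264: .96 at .05 and .37 at .01, adjusted if the value proves not to be partial);
   - report the smallest detectable effect (at 264: η² about .023 for power .70);
   - state that a non-significant hypothesis 5 will be reported with its 95% CI and not taken as evidence that the messages do not differ.

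The cost is text only. No extra participants are needed and the design is unchanged. If .01 stands, the stated power becomes less favourable.

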**Methods:**

A total of 264 participants will be involved, among the men’s relatives of women with verified germline mutations. The study entails a pre- post- evaluation with randomization of the participants in two conditions corresponding to the two messages.

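### The target of 264 and the calculated 132 are not reconciled, and the stated inputs at alpha .05 give 120; the stated sample size and power do not match, though the trial is not underpowered on its own inputs

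*Protocol article*

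**What the plan says.** The abstract of the protocol article (Methods) says "A total of 264 participants will be involved". The section Sample size and power calculation opens with the same figure: "Participants will be 264 males". That section then says the size comes from an a priori power analysis and lists the inputs as "partial η2 = .05, alpha lower than .05, power d (1-B) = .70". It adds: "Two groups, corresponding to the two experimental conditions of the study, and 7 covariates were included". The result is given as "The final estimated number of participants is 132, 66 in each group". The section also remarks that the number of covariates does not affect the total.

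Three other sections bear on the point:
- **Statistical analyses** assigns an ANCOVA to hypothesis 5, the primary comparison of the two messages. It also excludes men who do not complete T1 and T2.
- **Manipulation check** excludes men who fail the check.
- **Hypothesis 5**, as listed in the analysis plan, has two outcomes: intention and action.

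No rate of loss is given for either exclusion.

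**The concern.** If a power analysis determines the sample size, its result should equal the recruitment target, or a stated step should lead from one to the other. Here the target is exactly twice the result and no step is given. The factor of two could be an allowance for 50% loss, a figure per group taken for a total, or a slip. The text supports none of these over the others, and its own 66 per group speaks against the second.

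The calculated figure also cannot be recovered from its printed inputs at alpha .05.

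At stake is what a reader may rely on. The chance of missing the assumed effect on intention is about 26% with 132 men analysed and about 4% with 264. The section states 30% and gives no basis for choosing among the three.

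**Working it through.** **Inputs, all from Sample size and power calculation**
- Partial eta-squared .05
- Power .70
- Two equal groups and seven covariates
- Alpha: printed only as "alpha lower than .05"; taken here as exactly .05

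**Formula.** Power of the ANCOVA test of the group effect, from the noncentral F distribution:
- f² = η²/(1 − η²) = .05/.95 = .0526, so f = .229; for two equal groups d = 2f = .459
- noncentrality λ = N × f²
- df1 = 1; df2 = N − 2 − 7 = N − 9
- power = P(F(df1, df2, λ) > the central F critical value at alpha)

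**Attempt to reproduce 132**

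| N | λ | Critical F | Power |
|---|---|---|---|
| 118 | 6.21 | 3.93 | .695 |
| 120 | 6.32 | 3.93 | .702 |
| 132 | 6.95 | 3.92 | .744 |
| 264 | 13.89 | 3.88 | .960 |

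The smallest even N with power of at least .70 is 120, or 60 per group. The result is 120 with 0, 1, 3 or 7 covariates, so the article's remark about covariates is correct and they do not explain the gap. The normal approximation gives 59 per group, 118 in total. The printed 132 is 12 men, or 10%, above 120.

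**What would give a figure near 132** (none of these is stated)
- Alpha of .037 to .038: 132. Alpha .04: 130.
- f cut from .229 to .22: 130.
- Power .75 in place of .70: 134.
- 120 plus 10%: 120 × 1.10 = 132.
- f² taken as .05 itself: 126.

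Other readings move further away: one-sided testing gives 92, and alpha .025 gives 150.

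**From 132 to 264.** 132/(1 − .50) = 264, so an allowance for loss would have to be 50%. No such rate appears in the article.

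**The case against.** The case for leaving the text alone has four parts.

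**Planned power is a floor.** Both sizes exceed .70 at the stated effect, and recruiting more than the minimum is no error. This stands. A reader might infer from the mismatch that the trial is underpowered; on its own inputs it is not.

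**The 120 against 132 gap is small and depends on alpha.** The article does not fix alpha at .05, its wording suggests that the list of inputs is not complete, and the gap of 12 men is on the cautious side. This stands too. On its own it justifies a request for the exact inputs and little more.

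**Exclusions make over-recruitment sensible.** Men who fail the manipulation check or do not complete T1 and T2 will be dropped, so a target above 132 is understandable. This softens the conflict without removing it, because no rate is given and nothing says the surplus is there for that purpose. Condensation into an article does not explain it either: both figures are printed in one section.

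**A power of .96 must not be read too widely.** It requires all 264 men to be analysed, an eta-squared of .05 and independent participants, although the Sampling plan lets one woman invite several relatives. It applies to the intention score and not to action, which is whether the test is taken up. The section itself cites an earlier eta-squared of .01, at which power would be about .21 with 132 and .37 with 264. All of this stands and limits how the restated figure should be labelled.

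A further reading is tempting: with two targets in print, and analysts who know the groups (Blinding), the comparison might be tested at 132 and again at 264, which would inflate the type I error. The document does not support this. It contains no interim look, stopping rule or repeat test, and it names a single ANCOVA for hypothesis 5.

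**Conclusion.** The point holds in a limited form. The main defect is the unexplained factor of two between the recruitment target of 264 and the calculated 132. The lesser defect is that the stated inputs at alpha .05 give 120, so 132 rests on something not printed.

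The stated power of .70 belongs to neither published size: the figure is .74 with 132 analysed and up to .96 with 264. These values assume the ANCOVA on intention, eta-squared .05, two-sided alpha .05, equal groups and independent participants. The error is in the justification and does not show that too few men will be recruited. It still needs correcting, because the sample size and its power are figures the trial relies on and the correction is cheap.

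**What to change.** Rewrite the sample size paragraph as follows.

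1. Keep 264 as the single recruitment target, in agreement with the abstract.
2. State the exact alpha and every other input used.
3. Correct the calculated number: 120 in total (60 per group) at alpha .05. If 132 is kept, state the input that produces it.
4. State the loss expected from failed manipulation checks and from incomplete T1 and T2, and say whether this is why 264 exceeds the calculated number.
5. Give the power at the number expected to be analysed: .74 if 132, rising to .96 if all 264. Label it as applying to intention, at eta-squared .05, with independent participants, and not to the action outcome.

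The cost is one paragraph of text and an assumed rate of loss. The recruitment target stays at 264 and the analysis does not change.
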